## Abstract

**Background:**

Insomnia is very common in current society, and patients are often accompanied by a certain degree of anxiety, depression, etc. Recent studies have found that the hypothalamic-pituitary-adrenal (HPA) axis excitement-inhibition state is an important indicator of sleep quality. Wrist-ankle acupuncture (WAA) is safe and effective for insomnia. Based on WAA theory, the acupressure wrist-ankle straps are portable WAA point compression straps that can treat diseases by automatically applying pressure to the treatment location and being operated by patients themselves. We design this trial to evaluate the clinical effect of the acupressure wrist-ankle strap in the treatment of mild insomnia patients with anxiety disorders.

**Methods/design:**

This trial is a parallel-design, patients-assessor blinded, randomized, sham-controlled. In total, 114 patients diagnosed with mild insomnia and anxiety disorders will be randomly assigned into two groups, the acupressure wrist-ankle strap group or the non-acupressure wrist-ankle strap group; they will receive treatments for eight weeks with five sessions each week. Rating scales, sleep monitors, and laboratory tests will be used to observe the clinical effect. From the perspective of the circadian secretion of peripheral blood-related hormones in the hypothalamic-pituitary-adrenal (HPA) axis, the possible mechanism of acupressure wrist-ankle straps for treating insomnia is studied.

**Discussion:**

The results of this study will confirm the efficacy of acupressure wrist-ankle strap in treating mild insomnia patients with anxiety disorder and whether its mechanism is related to the HPA axis. The acupressure wrist-ankle strap may become a pure physical, no side effect treatment of mild insomnia.

**Trial registration:**

Chinese Clinical Trial Registry ChiCTR2000039352. Registered on 24 October 2020.

## Background

After a lapse of 9 years, the British Psychopharmacological Association (BAP) updated its consensus on treating insomnia, parasomnia, and circadian rhythm disorders in 2019. The consensus mentioned that about half of all patients with diagnosed insomnia have at least one comorbidity of mental disorder [1]. Insomnia patients are often accompanied by a certain degree of anxiety, depression, and other bad moods. The specific manifestations of insomnia patients with an anxiety disorder include insomnia with significant anxiety symptoms or emotional disorders such as nervousness, worry, and irritability [2]. Clinical studies found that about 50% of insomnia patients are accompanied by mental disorders [3, 4]. Compared with non-anxiety insomnia patients, insomnia patients with anxiety have significantly reduced sleep efficiency, total sleep time, and percentage of slow-wave sleep, which significantly reduces patients’ quality of life and brings severe social dysfunction and economic burden [5, 6].

Although the pathogenesis of insomnia has not yet been fully understood, studies [7] have found that the excitation-inhibition state of the hypothalamic-pituitary-adrenal (HPA) axis is an important indicator of sleep quality. The HPA axis is mainly composed of the hypothalamus, pituitary gland, and adrenal glands, and its activity is regulated by corticotrophin-releasing hormone (CRH). CRH promotes the secretion of adreno-cortico-tropic-hormone (ACTH) from the pituitary. ACTH is released into the blood and reaches the adrenal gland through systemic circulation, prompting the adrenal cortex to release glucocorticoids and cortisol (CORT). ACTH can improve the irritability of the cerebral cortex and is an integral part of the sleep-wake regulation mechanism. Many monoamine neurotransmitters, such as serotonin (5-HT) and norepinephrine (NE), also play an essential role in the regulation of the HPA axis [8].

At present, hypnotics recommended by the guidelines for insomnia include benzodiazepine receptor agonists (BZRA) (including non-benzodiazepines and benzodiazepines) or melatonin receptor agonists (e.g., ramelteon), sedative antidepressants (trazodone, mirtazapine, fluvoxamine, and doxepin). The latter is especially suitable for insomnia patients with depression or anxiety or both of them. However, patients may have dizziness, drowsiness, cognitive dysfunction, apnea, and other adverse reactions after taking such drugs. In addition to own adverse drug reactions, there were also insomnia rebound and withdrawal reactions [1, 3, 9]. Patients with mild insomnia have occasional insomnia, which often has little effect on work, and often does not require drug treatment. It can be improved by non-drug treatment represented by sleep hygiene education and cognitive behavioral therapy for insomnia (CBTI) [10], and most of them are against medication. Therefore, it is of great significance for patients with mild insomnia to develop a purely physical, easy-to-operate, non-invasive, non-toxic, and side-effect and repeated use of drug replacement therapy.

Wrist-ankle acupuncture (WAA) is a unique acupuncture therapy performed through the subcutaneous insertion of needles at points on the wrist and ankle regions [11]. WAA does not induce pain or “needling sensation.” The acupressure wrist-ankle strap (China patent ZL201420475426.8) is a device developed based on WAA therapy. Unlike WAA, the acupressure wrist-ankle strap is non-invasive, recyclable, and does not need an acupuncturist to operate. Patients can wear it on their wrists or ankles like wearing watches. Clinical studies have shown that WAA has a good effect on insomnia [12–14]. However, there is no clinical randomized controlled study to prove the efficacy of the acupressure wrist-ankle strap for insomnia and whether the acupressure wrist-ankle strap and WAA have a similar effect for insomnia. Our clinical experience indicates that patients with mild insomnia can quickly calm down and enter a sleep state after using the strap. If the proposed RCT can verify our hypothesis that acupressure wrist-ankle strap is also effective for insomnia, a new convenient and effective physical therapy is available for insomnia patients with anxiety disorder.

## Methods/design

### Study design

This study is a two-armed, double-blind, randomized, sham-controlled clinical trial aiming to explore the efficacy of the acupressure wrist-ankle strap for insomnia patients with anxiety disorder.

A total of 114 participants, from the department of acupuncture and moxibustion and the department of internal medicine of traditional Chinese medicine of Shanghai Changhai Hospital, diagnosed with mild insomnia and anxiety disorder following *Guidelines for the Diagnosis and Treatment of Insomnia in China* formulated by the Chinese Sleep Medicine Congress (CSMC, 2017 revised version) [3] and *Expert Consensus on Diagnosis and Treatment of Anxiety and Depression in General Hospitals* formulated by Anxiety disorder cooperation group, Psychiatry Branch, Chinese Medical Association (2012 revised version) [15] will be randomly assigned to two equal groups with 57 patients in each group, including acupressure and non-acupressure wrist-ankle strap group. The outcomes include scales, objective parameters detected by device (wActiSleep-BT Actigraph equipment), and laboratory tests, which will be used to observe the efficacy of the strap on insomnia patients and study its possible mechanism of circadian secretion of related hormones in peripheral blood of hypothalamic-pituitary-adrenal axis (HPA axis). Our study will last 13 weeks in total. The protocol has been registered on the Chinese Clinical Trial Registry (identifier: ChiCTR2000039352) and will be conducted following the Helsinki declaration. This trial will be reported according to the Consolidated Standards of Reporting Trials (CONSORT) statement [16]. The study flowchart is summarized in Fig. 1.

**Fig. 1 Fig1:**
[figure not shown]
Flowchart of the trial

### Participants

Patients meeting the *Guidelines for the Diagnosis and Treatment of Insomnia in China* formulated by CSMC in 2017 and *Expert Consensus on Diagnosis and Treatment of Anxiety and Depression in General Hospitals* formulated by anxiety disorder cooperation group, Psychiatry Branch, CMA in 2012 will be recruited.

#### Inclusion criteria

Eligibility for participation requires each of the following criteria to be met:
Symptoms comply with both the *Guidelines for the Diagnosis and Treatment of Insomnia in China* formulated by the CSMC in 2017 and *Expert Consensus on Diagnosis and Treatment of Anxiety and Depression in General Hospitals* formulated by anxiety disorder cooperation group, Psychiatry Branch, CMA in 2012The occurrence of insomnia was 3 times (including) to 5 times per weekThe Pittsburgh Sleep Quality Index (PSQI) score was 7 to 11 [17], and the Hamilton Anxiety Scale (HAMA) score > 14 [18]Age 18–70 years at the time of enrolment (either sex)Have not received WAA or other similar treatmentsPrefer physical therapy rather than medicationSigned informed consent

#### Exclusion criteria

Patients who meet any of the following criteria will be excluded:
Suffering from insomnia caused by mental diseases or drugsDependence or abuse of alcohol or other substancesCurrently pregnant or lactatingHaving any severe disease of the cardiovascular, liver, kidney, hematopoietic system, and psychiatric disordersAllergic to the material of the wrist-ankle strapsHave taken hypnotic and sedative drugs within one month

#### Dropout criteria

The researcher decides to withdraw from the trial:
The patient’s condition progressed or continues to deteriorate during the trial, and the clinical trial should be stopped according to the doctor's judgmentDuring the trial period, the patient has severe complications or notable physiological changes, and it is not suitable to continue the testSerious adverse events occurred during the trial periodThe patient has poor compliance during the trial period, and the treatment dose was less than 80% or more than 120%

Patients quit the trial by themselves:
During the trial period, patients are unwilling to continue the treatment or take hypnotic-sedative drugs by themselves due to various reasons and actively propose to withdraw from the clinical trialAlthough the patients do not explicitly propose to withdraw from the trial, they might fall out naturally due to loss of follow-up

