#### Primary outcome

The primary outcome is the Pittsburgh sleep quality index (PSQI) global score, which evaluates a patient's general sleep quality in the past month. The PSQI consists of 19 self-assessment questions and 5 questions assessed by sleep partners. Only 19 self-assessment questions will be scored. The 19 self-assessment questions constitute seven factors from 0 to 3 points. The cumulative score of each factor component is the total score of the PSQI. The total score ranges from 0 to 21. A higher score means worse sleep quality [21]. The PSQI will be assessed at baseline, 4, 8 weeks after randomization and follow-up period.

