#### Secondary outcomes

##### PSQI component scores

The PSQI component scores include seven domains, using 0, 1, 2, and 3 points to evaluate the patient's duration of sleep, sleep disturbance, sleep-onset latency, daytime dysfunction due to night sleep, sleep efficiency, need for medications to sleep, and overall sleep quality [17], which will be assessed at baseline, 4, 8 weeks after randomization and follow-up period.

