In this trial, the patients with mild insomnia prefer physical therapy rather than medication, and there is no high risk without other treatments. Therefore, it is ethically possible for us to include a control group that receives just CBTI. This trial is a rigorously designed randomized controlled, double-blind trial. The design of the non-acupressure wrist-ankle strap, the wrist-ankle strap instruction manual, and follow-up appointments ensure the accuracy of the blind method of this trial. To ensure the quality of this research, before the research officially starts, we conducted a pre-experiment first, consult experts and literature to optimize the test plan based on the pre-test situation, and submitted the study protocol to the medical ethics committee for review and approval; each stage of the trial has an independent researcher to supervise the subject and collect feedback in time; all the research participants, including researchers, receptionists, and data processors, will be trained to ensure the smooth implementation of the trial.

The study aims to provide evidence-based medical evidence for the prevention and treatment of insomnia by acupressure wrist-ankle strap and promotes WAA clinical application. The result of this trial is expected to confirm that the new type of acupressure wrist-ankle strap can significantly improve the sleep quality and anxiety disorder of patients, reduce the suffering of patients, and improve the quality of life; it can also shorten the latency to fall asleep, increase the total sleep time, reduce the number of arousals and duration, improve sleep efficiency; it can reduce ACTH, CORT, 5-HT, and NA in the peripheral blood of patients with insomnia, thereby improving sleep quality.

In view of the above considerations, this study intends to sort out and summarize the clinical data of the new type of acupressure wrist-ankle strap for mild insomnia patients with anxiety disorder in this research group and form a standardized treatment plan. A strictly designed randomized controlled study method will be used to compare the improvement of acupressure wrist-ankle strap and non-acupressure wrist-ankle strap on the patients, to verify its efficacy further and explore the possible mechanism of action, to enrich the treatment of insomnia, improve its clinical efficacy, and lay the foundation for the popularization and application of the acupressure wrist-ankle strap.

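### The dropout criteria end trial participation, not just strap use, after worsening or poor compliance, so scheduled outcome visits are lost and LOCF fills the gaps

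*Protocol article*

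**What the plan says.** The Dropout criteria contain two lists. The first opens with "The researcher decides to withdraw from the trial". It covers deterioration that the doctor judges a reason to stop, severe complications or marked physiological change, serious adverse events, and "poor compliance during the trial period, and the treatment dose was less than 80% or more than 120" per cent. The second covers patients who leave of their own accord: those who no longer want the treatment, or take hypnotics or sedatives themselves, and ask to leave; and those lost to follow-up.

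On assessment, the Primary outcome section says "The PSQI will be assessed at baseline, 4, 8 weeks after randomization and follow-up period". HAMA and actigraphy follow the same timetable. No section says whether a withdrawn patient still attends. The Statistical analysis section replaces missing data by LOCF. The Sample size section allows for 20% dropout and does not split it by arm.

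The PSQI "evaluates a patient's general sleep quality in the past month". It has seven components, one of them "need for medications to sleep", and they are added up: "The cumulative score of each factor component is the total score of the PSQI".

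On wearing time, the abstract gives five sessions a week for eight weeks. The two strap-group sections under Interventions give daily wear over four two-week courses.

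**The concern.** The first list uses one act, withdrawal from the trial, for events that need only affect use of the strap. Read plainly, a patient who worsens or falls outside the compliance band is no longer observed, although PSQI, HAMA and actigraphy could still be obtained.

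All of these events occur after randomisation, and their frequency may depend on the arm. LOCF keeps the withdrawn patient in the comparison, but with a score taken before the event. For a patient withdrawn because of worsening, that score may well be better than the one that was never collected. No later choice of analysis can recover a week-8 score that was not taken, so this is a matter of conduct that the protocol has to settle. What is at stake is the primary between-arm comparison of the PSQI global score.

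**Working it through.** **1. The plan's own figures.** Inputs from the Sample size section: means 6.125 (active) and 8.625 (control), SD 3.60 taken as stated, z values 1.96 and 1.28, equal allocation.

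- Planned difference: 8.625 − 6.125 = 2.5.
- n per group = (1.96 + 1.28)² × 3.60² × 2 / 2.5² = 10.4976 × 12.96 × 2 / 6.25 = 43.5, so 44 by the normal formula. A t-based calculation gives 45 (power 0.896 at 44, 0.903 at 45).
- With 20% dropout: 45 / 0.80 = 56.25, so 57 per group and 114 in total.

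The stated 45, 57 and 114 reproduce. The point does not change them. It uses only the 2.5-point difference and the 20% dropout.

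**2. What LOCF carries forward.** A patient withdrawn before week 4 has only a baseline PSQI, which the Inclusion criteria limit to 7–11. A patient withdrawn between weeks 4 and 8 carries the week-4 score. Let g be the unseen week-8 score minus the carried score.

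**3. Error in the difference.** Let qA and qC be the shares withdrawn in the active and control arms, with the same g in both. Each LOCF mean is too low by g × its share, so for active minus control:

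LOCF difference − true difference = −g·qA + g·qC = g × (qC − qA).

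The planned difference on this scale is −2.5. A positive error therefore shrinks the apparent benefit and a negative one enlarges it.

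**4. Numbers.** Neither g nor the split by arm is in the documents. Both are assumptions. The shares below average 20%, the planned dropout.

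| g | 10% active, 30% control | 15% active, 25% control | 20% each | 30% active, 10% control |
|---|---|---|---|---|
| 1 | +0.2 | +0.1 | 0 | −0.2 |
| 2 | +0.4 | +0.2 | 0 | −0.4 |
| 3 | +0.6 | +0.3 | 0 | −0.6 |
| 4 | +0.8 | +0.4 | 0 | −0.8 |

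Against 2.5 points, 0.2 to 0.8 is 8% to 32%. The table treats all planned dropout as having the same g. If only half of it did (5% and 15%), the error would be 0.1 to 0.4 points.

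**5. The compliance band.** Counting one wearing as one session (the article does not define the unit of dose):

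- Five a week for 8 weeks is 5 × 8 = 40 sessions; 80%–120% of 40 is 32 to 48.
- Daily wear over four two-week courses is 4 × 14 = 56 sessions; 80%–120% of 56 is 44.8 to 67.2.
- 56 / 40 = 140% and 40 / 56 = 71%.

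Full adherence to either schedule falls outside the band built on the other. As written, the rule could withdraw patients who follow one of the protocol's own schedules.

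**The case against.** The strongest reply is that this is a condensed article and that visits after withdrawal may be set out in the full protocol. That has weight: the article does not state that assessments stop. It is the plain reading of a stated rule whose object is the trial. If the full protocol keeps the visits, the repair is one clarifying sentence.

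A second reply is that unequal withdrawal is conjecture. Patients are to be blinded, and app attendance and telephone calls support wear in both arms. That stands as far as direction and size go: neither can be fixed from the documents, and with equal shares and equal g the error is zero.

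Several stronger readings are tempting and are not supported:

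- *That starting a hypnotic removes a patient by rule.* These patients are in the second list and leave only if they ask to.
- *That the PSQI medication component is zero by design.* The one-month drug exclusion applies at entry, whereas later PSQI assessments look back over time on trial. A user who stays can score. Low scores are to be expected because entrants "prefer physical therapy rather than medication", which is a feature of the population.
- *That withdrawn patients leave the analysis.* The article does not say so, and LOCF suggests they stay in. A bias computed from the mean of the remaining patients is therefore not that of the planned analysis.
- *That poor compliers have the worst outcomes.* Nothing in the article shows this. The link to a poor score is direct for deterioration only.

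**Conclusion.** The point holds as a defect in the rule for who remains under observation. The Dropout criteria do not separate stopping the strap from leaving the trial, no section preserves later assessments, and LOCF then supplies earlier scores. On the assumptions shown (10% and 30% withdrawn, a common g of 1 to 4), the primary difference could be off by 0.2 to 0.8 points out of 2.5, in either direction depending on which arm loses more. If g differs between arms, the error is gC·qC − gA·qA, which need not vanish with equal shares. The figures illustrate the possible size and do not predict it. The conflict over the base of the 80%–120% band follows directly from the article's two schedules, if one wearing counts as one session.

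**What to change.** Amend the Dropout criteria as follows:

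- State that the events in the researcher's list may end or change use of the strap but do not end outcome assessment. Clinical decisions on stopping or referral stay as they are.
- Keep the scheduled week-4, week-8 and follow-up PSQI, HAMA and actigraphy assessments unless the patient withdraws consent, and analyse patients as randomised with the values collected.
- Record a dose outside 80%–120% as adherence data, and remove it as a reason for withdrawal from the trial.
- Record the start of hypnotics (yes/no and date) in both arms, in addition to the PSQI medication component. That component stays in the global score, so the primary outcome is unchanged.
- Reconcile the abstract's five sessions a week with the daily wear in the strap-group sections, and state which count is the base of the band.

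The cost is a protocol amendment and some effort to retain these patients. The visits are already planned for 57 per arm, and the article reports recruitment as still open. Patients who have asked to leave and withdrawn consent will not be recovered, so some missing data will remain.

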### Randomization, allocation concealment

A random sequence list is generated using stratified block randomization design and SAS 9.4 (SAS Institute Inc., Cary, NC, USA). The sequence is stratified by gender and age. This trial has an independent statistician assigning the eligible patients to the corresponding intervention code based on the list, who is not be involved in recruitment, implementation, data collection, and data analysis of this trial. All of the random code information is kept by a certain person and stored in sealed opaque envelopes. When an eligible patient is enrolled in the group, the statistician will randomize the patient according to the above method, and the corresponding box with a wrist-ankle strap will be given to the researcher who will be responsible for informing patients the details about the implementation, the wrist-ankle straps used in both groups will have the same packaging. The allocation concealment procedure will not be exposed until the clinical trial is finished.

### Blinding

All the patients, outcome assessors, and data analysts will be blinded to treatment allocation. Every patient of the two groups will receive the same packaging box in the above envelope after entering the group according to the allocation method, which contains the strap (acupressure wrist-ankle strap or non-acupressure wrist-ankle strap) and its instructions, which will guide patients themselves on how to use the straps and informed them related precautions, including the size of the straps, tightness, selection, and adjustment of compression devices and wearing time. To prevent the patients from communicating, we will use follow-up appointments to ensure that the patients will stagger their visits and avoid communication. When the patient withdraws from the trial due to various reasons, emergency unblinding is allowed.

